#### Bone mineral density

Total hip, femoral neck and lumbar spine (L1–L4) aBMD (g/cm^2^) will be assessed using DXA (Lunar Prodigy, GE Lunar Corp., Madison, WI, USA) using software version 12.30.008. The short-term coefficient of variation (CV) for aBMD measures range from 0.6 to 1.0% within our laboratory.

#### Volumetric BMD, bone geometry and strength

Proximal (66%) radial and tibial cortical vBMD (mg/cm^3^), cortical area (mm^2^), total bone area (mm^2^), medullary area (mm^2^) and polar Strength Strain Index (SSIpolar, mm^3^), and distal (4%) radial and tibial total and trabecular vBMD (mg/cm^3^), total bone area (mm^2^) and the Bone Strength Index (BSI, mg^2^/mm^4^) of the non-dominant upper limb and dominant lower limb will be assessed using pQCT (XCT 3000, Stratec Medizintechnik GmbH, Pforzheim, Germany). Briefly, tibial length will be determined by measuring from the distal edge of the medial malleolus to the medial joint cleft of the knee and radial length will be determined by measuring ulnar length from the ulnar styloid process to the olecranon. After obtaining a scout-view slice of the distal endplate of the radius or tibia, scans will be performed at the 4% and 66% sites. The slice thickness will be 1 mm and voxel size will be 0.5 mm at a scanning speed of 20 mm/s. All pQCT bone and body composition parameters will be assessed using BoneJ [60] ImageJ-plugin (rsbweb.nih.gov/ij) as previously reported [61]. Distal radial and tibial (4%) total bone area and density will be analysed based on thresholding at 169 mg/cm^3^, with trabecular density assessed using a threshold of 480 mg/cm^3^. BSI will be calculated as follows: BSI = total area multiplied by the square of total vBMD [62]. For the proximal radius and tibia (66%), the periosteal surface will be determined based on a threshold of 280 mg/cm^3^, and cortical bone a threshold of 710 mm/cm^3^. Medullary area will be calculated by subtracting cortical area from total area. SSIpolar will be determined using the bone threshold of 480 mg/cm^3^ [63]. The short-term CVs for repeated measures in a sample of healthy premenopausal women range from 0.9 to 2.2% for the 4% radius, 0.7 to 2.5% for the 4% tibial and 0.6 and 1.8% for the 66% tibial outcome measures [64].

#### Body composition

Total and regional (arms and legs) LBM (kg), FM (kg) and percentage body fat will be assessed by DXA as described above. The short-term CV for LBM and FM repeated measures range from 1.0 to 1.7% within our laboratory. Muscle and subcutaneous fat cross-sectional area (CSA) and muscle density (as a measure of intermuscular adiposity) at the proximal (66%) radius and tibia will be assessed using pQCT. Thresholds of − 40 to + 40 mg/cm^3^ hydroxyapatite density will be used for estimating subcutaneous fat CSA. Muscle CSA will be estimated by subtracting the total bone CSA and subcutaneous fat CSA from the total area of the 66% tibia or radius. The following CVs have been reported for muscle CSA (radius, 2.1 to 5.3%; tibia, 2.5 to 3.7%), muscle density (radius, 1.4 to 3.2%; tibia 0.7 to 3.2%) and subcutaneous fat CSA (radius, 2.4 to 3.2%; tibia, 6.0 to 6.3%) for repeated measures in a sample of postmenopausal women [65].

#### Muscle strength

Muscle strength will be obtained via chest press (BodySolid, Powerline Smith Machine PSM144X, Forest Park, IL, USA), leg press (Synergy Omni Leg Press S-31-OPD, Yatala, QLD, Australia) and seated row (Nautilus tower pulley system, F3ATFS, Independence, VA, USA) three-repetition maximum (3-RM) protocols [53]. The 3-RM protocols assess the maximum weight that can be lifted for three repetitions while maintaining correct form and technique and were selected rather than one-repetition maximum protocols to reduce participant exertion. Prior to attempting these protocols, participants will complete a 5-min aerobic warm-up. Thereafter, each participant will perform a warm-up set of eight to 10 repetitions with a light load. The participant will then complete six to eight repetitions at a heavier weight. The load will be increased incrementally until only three repetitions can be completed. A 2–3-min recovery period will be provided between each set. The 3-RM result will be used in a formula to calculate each participant’s one-repetition maximum [66]. The 3-RM protocol has been shown to have a test-retest intraclass correlation coefficient (ICC) of 0.97 in a sample of untrained men [67] and strongly correlates with 1-RM results [68].

Maximal muscle (grip) strength will be assessed using a digital grip-strength dynamometer (Jamar Plus Digital, Lafayette Instrument Company, IN, USA) [69]. The participant will be seated with their foreman resting on the arm of chair while maintaining a 90° angle at the elbow. Participants will be asked to squeeze the dynamometer maximally. Six trials will be completed (three with each hand alternating) with the single highest score recorded. A CV of 6.3% was reported for grip-strength repeated measures with the same device in a sample of advanced lung and gastrointestinal cancer patients [70].

#### Functional capacity

Functional capacity will be assessed using the 30-s sit-to-stand, timed-up-and-go (TUG) with cognitive task test, the four-square step test, the Berg Balance Scale, the 4-m usual walk and the 400-m walk. The 30-s sit-to-stand, four-square step test and 4-m usual walk will be performed in triplicate, with the best result recorded. All other tests will be performed once.

The 30-s sit-to-stand test measures lower-limb muscle strength and function [71]. Participants begin in a seated position with their arms folded across their chest on a chair without arms. Participants are instructed to stand fully upright and then return to a seated position as many times as possible in 30 s. This test was observed to have a test-retest ICC of 0.84 in a sample of community-dwelling men aged 60 years and over [71].

The TUG with cognitive task test is a measure of dynamic balance and dual-tasking [72]. Participants will be seated in a chair (height 45 cm) that will be placed at the end of a 3-m walkway. Once instructed to begin, the participant will stand up, walk at a regular pace for 3 m, turn, walk back to the chair and sit down. During this task, the participant will be provided with a mental arithmetic task (e.g. counting backwards from 100 by 3’s from a random number) and the number of correct digits will be recorded. A stopwatch will be used to record the time taken (to the nearest ms) to complete each test. This test was observed to have an interrater ICC of 0.99 [73].

The four-square step test is a measure of dynamic balance and stepping speed in four directions [74]. Participants will be instructed to step forward, sideways, and backwards over four canes resting flat on the floor in a cross formation in a clockwise sequence and then back to in an anticlockwise sequence. The participant will be instructed to complete the test as fast as possible without touching the raised canes, and to face forward during the entire sequence. They will also be instructed to ensure that both feet make contact with the floor in each square. The time (to the nearest ms) taken to complete the sequence will be measured with a stopwatch. This test has been observed to have an interrater and test-retest ICC of 0.99 and 0.98, respectively, in a sample of community-dwelling adults aged 65 years and over [74].

The Berg Balance Scale is an overall measure of balance including both dynamic and static components [75]. The test rates participants on 14 different tasks on an ordinal scale ranging from zero (unable to perform the task) to 4 (performs the task independently). Assessments include variations of sitting, standing, reaching, leaning, turning and stepping. The scores of the 14 tasks are summed to produce a total score ranging from 0 to 56 points. Higher scores indicate better performance. This test was observed to have an interrater and test-retest ICC of 0.98 and 0.97, respectively, in a sample of adults aged 65 years and over [75].

The 4-m usual walk is a measure of gait speed [76]. Participants will be instructed to walk at a usual pace between two cones 8 m apart (2-m acceleration zone, 4-m timed zone and 2-m deceleration zone). Time will be recorded when the participant’s front foot enters the timed zone and stopped when their front foot exits the timed zone. The time (to the nearest ms) to complete the timed zone was recorded with a stopwatch. This method has an ICC of 0.96 within our laboratory.

The 400-m walk test provides an estimate of cardiorespiratory fitness [77]. Participants will be instructed to walk as fast as possible between two cones placed 20 m apart (turning when they approach each cone). The time (to the nearest ms) taken to complete 10 laps (400 m) will be recorded. This test was observed to have a test-retest ICC of 0.95 in a sample of middle-aged women [78].

#### Biochemical, lipid and lipoprotein measures

Fasted, resting, morning blood samples will be collected at a commercial pathology clinic and sent to a central laboratory accredited by the National Association of Testing Authorities Royal College of Pathologists Australasia. The following parameters will be assessed using standardised techniques: creatinine, albumin, inorganic phosphate and corrected calcium. Fasting plasma glucose will be assessed using the hexokinase method (Roche Diagnostics, Mannheim, Germany). Total cholesterol, high-density lipoprotein cholesterol and triglycerides will be determined using an enzymatic colorimetric method (Roche Diagnostics, Mannheim, Germany). Low-density lipoprotein cholesterol will be calculated using Friedewald’s formula. The estimated glomerular filtration rate (eGFR) will be calculated using the participants’ serum creatinine, age and sex according to the abbreviated ‘modification of diet in renal disease’ formula, which is now used by most laboratories in Australia:$$ \mathrm{eGFR}\left[\mathrm{ml}/\left(\min\;1.73\;{\mathrm{m}}^2\right)\right]=175\times {\left[\mathrm{serum}\  \mathrm{creatinine}\left(\upmu \mathrm{mol}/\mathrm{l}\right)\times 0.0113\right]}^{-1.154}\times \mathrm{age}{\left(\mathrm{years}\right)}^{-0.203}. $$

High-sensitivity C-reactive protein (CRP) will be assessed using an immunoturbidimetric assay (Roche Diagnostics, Mannheim, Germany). Total prostate-specific antigen (free and complexed) will be assessed via immunoassay (Roche Diagnostics, Mannheim, Germany).

Serum aliquots will also be collected and stored at − 80 °C so that the following parameters can be assessed in a single batch at the completion of the study if sufficient funding is obtained: serum insulin, serum 25-hydroxyvitamin D (25(OH)D), IGF-1, serum adiponectin and resistin, and a battery of pro-inflammatory and anti-inflammatory cytokines, including interleukin (IL)-6, IL-1β, IL-8, tumour necrosis factor (TNF)-α and IL-10.

#### Blood pressure

Blood pressure will be assessed three times using an automated machine (TM-2655P, A&D, Tokyo, Japan) [79] after a 10-min rest, with 1-min intervals between trials. The mean of the second and third measures will be used.

#### Cognitive function

Previous research has shown that ADT use is associated with cognitive decline, particularly in the domains of verbal memory, visuomotor function, attention and executive function [80]. Thus, this study will include a number of established and valid cognitive tests to assess the different cognitive domains. The CogState Brief Battery computerised test (http://cogstate.com/) will be administered to assess cognitive function including psychomotor function, attention, learning, reaction time, processing speed, visual attention and working memory [81, 82]. The CogState battery involves five computerised tests (Groton maze, detection task, identification task, one card learning task, one back task) conducted in a quiet environment, with scripted instructions and a practice attempt prior to completing each task.

The Rey Auditory Verbal Learning Test will be administered to assess memory and learning [83]. A list of 15 common words is read to the participant five times, with the participant asked to immediately recall as many words as possible following each recital. An interference list is then presented, after which the participant must recall words from the original list. Following a 20-min delay, during which other non-verbal tests are conducted, the participant is asked to recall the original list again. Finally, the participant will be asked to visually identify the words from the original list from a list of 50 words. Participants are scored on the total number of words recalled in trials 1–5, total number recalled after interference, loss after interference number (trial 5 minus trial 2) and long-delay free recall.

The Trail Making Test (Parts A and B) will be administered to assess executive function [84]. Participants will be instructed to accurately draw lines to connect circled numbers in sequential order as fast as possible (Part A). Participants will then be instructed to draw lines to connect circled numbers and letters in an alternating numeric and alphabetic order (Part B).

The Digit Span Test measures working memory and will be administered forwards and backwards to assess short-term memory and working memory, respectively [85]. In the first condition, the researcher presents the participant with a string of non-sequential numbers which gradually increase in length, which the participant must then immediately recall in the same order in which they were presented. In the second condition, the researcher also presents the participant with a string of non-sequential numbers which gradually increase in length, but the participant must immediately recall them in the reverse order to which they were presented.

The National Adult Reading Test will be administered to calculate verbal, performance and full-scale intelligence quotes as an estimate of cognitive reserve [86]. The test comprises of 50 irregular words which are read aloud by the participant. The number of errors regarding pronunciation are recorded.

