### Primary and secondary outcome measures

The primary outcome for this study will be changes in proximal femur and lumbar spine aBMD. Secondary outcomes will comprise: changes in 4% and 66% tibial and radial vBMD, bone structure and strength, total body and regional body composition, muscle strength, functional capacity, cardiometabolic health, inflammatory biomarkers, HR-QoL and cognitive function.

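### The Rey Auditory Verbal Learning Test loss-after-interference score is defined from two recalls that both precede the interference list, so as written it measures learning gain

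*Protocol article*

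**What the plan says.** The Cognitive function section sets out the order of the test. First come the learning trials: "A list of 15 common words is read to the participant five times", with immediate recall after each reading. Next, "An interference list is then presented, after which the participant must recall words from the original list". A delayed recall follows 20 minutes later, and then a recognition step.

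The scoring sentence begins "Participants are scored on the total number of words recalled in trials 1–5, total number recalled after interference" and finishes with "loss after interference number (trial 5 minus trial 2) and long-delay free recall". That makes four scores: total learning, recall after interference, loss after interference, and long-delay recall.

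Cognitive function is a declared secondary outcome. The section on primary and secondary outcome measures closes its list with "cardiometabolic health, inflammatory biomarkers, HR-QoL and cognitive function". Table 2 schedules the test at baseline, 26 weeks and 52 weeks.

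**The concern.** A loss score needs a before and an after. The bracketed formula takes both terms from the learning phase, so the label and the calculation describe different things. The label promises a measure of forgetting, where a high value is bad. The calculation gives a measure of acquisition, where a high value means more words were picked up between the second and fifth readings.

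If the formula were carried into a scoring sheet or a derivation program as printed, the trial would report a group comparison under a name that does not describe it, and readers would interpret a higher value as poorer retention. The section names verbal memory among the domains reported to decline with androgen deprivation, so this test bears on a question the trial set out to address.

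**Working it through.** The protocol gives no numerical result to reproduce here. The check is one of definitions, followed by arithmetic on assumed scores.

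**Order of recalls, from the Cognitive function section**

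1. Learning trials 1 to 5: the list is read and recalled five times.
2. The interference list is presented.
3. The original list is recalled after interference. The scoring sentence treats this as a score of its own, separate from trials 1 to 5.
4. The original list is recalled after the 20-minute delay.

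Trials 2 and 5 both fall in step 1. Nothing elsewhere in the article renumbers the trials or corrects the formula.

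**Notation**

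Let T2 and T5 be the words recalled at learning trials 2 and 5, and P the words of the original list recalled after the interference list.

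- Printed score: S = T5 − T2
- Loss after interference: L = T5 − P
- Difference: S − L = P − T2

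The two scores agree only for a man whose post-interference recall happens to equal his second learning trial. P does not appear in S, so an intervention effect confined to retention (P changes, T2 and T5 do not) would leave S unchanged.

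**Assumed scores, for illustration only (not from the protocol)**

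| Man | T2 | T5 | P | S = T5 − T2 | L = T5 − P |
|---|---|---|---|---|---|
| A | 8 | 12 | 12 | 4 | 0 |
| B | 12 | 12 | 8 | 0 | 4 |
| C | 6 | 12 | 11 | 6 | 1 |

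Man A forgot nothing and man B forgot four words, yet the printed score gives A the larger loss. The ranking of A and B is reversed. Man C is credited with a loss of 6 when he lost 1 word.

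**How S responds to better learning**

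- T5 rises by 2, T2 unchanged: S rises by 2.
- T2 and T5 both rise by 2: S is unchanged.
- T2 rises by 2, T5 unchanged: S falls by 2.

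The printed score therefore has no fixed direction relative to benefit. The correct score is not immune to this either: if T5 rises by 2 and P stays the same, L also rises by 2.

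**The case against.** The strongest reply is that this is a slip in a bracket and not a scoring rule. The label, the test sequence and the neighbouring score for recall after interference all make the intended quantity clear. The section presents its instruments as established ones, and this test carries a citation that may well give the standard scoring. The article cannot show what the database computes. All of that stands, and it makes the consequence conditional: there is harm only if the score is derived as printed. It does not remove the contradiction, because the formula is a positive statement about how an outcome is scored and not a detail left to an analysis plan.

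The reply also points to the limited reach. Total words over trials 1 to 5, recall after interference and long-delay recall are correctly described and cover learning and retention directly. The test is one of several cognitive instruments. The primary bone density outcome is not involved, and the sample size section makes no power claim about cognition. This stands in full.

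A reader might go further and infer that the error reverses the direction of effect, so that a cognitive benefit would be reported as harm. The document does not support that. As the working shows, better learning can raise, lower or leave unchanged the printed score, depending on which trial improves. The three unaffected scores would also sit beside any misleading result and could contradict it. Nor does the article show that any score has already been derived wrongly. Its Trial status section says only that recruitment and the intervention are in progress.

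**Conclusion.** The definition is wrong as written. On the article's own numbering, the score labelled as loss after interference contains no post-interference recall. It measures the gain from the second to the fifth learning trial and can order participants differently from a true loss score.

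The size is modest: one of four listed scores, from one test, within a secondary outcome. The conclusion that the definition contradicts its label rests only on the test sequence and scoring sentence in the Cognitive function section. The conclusion that a wrong score would be reported rests on the further assumption that the printed formula is the one applied, which cannot be settled from the article. The worked scores are invented to show what the two formulas do and do not estimate how far they would diverge in this trial.

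**What to change.** Replace the bracketed formula with trial 5 minus the number of words of the original list recalled after the interference list. State that higher values mean greater loss.

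Confirm that the scoring sheet and the database derivation use this definition, and recompute the score if any values have been derived from trial 2. Do this before the groups are compared. The Randomisation and blinding section says that, apart from the scan assessments, the researchers who carry out testing know the allocation, so the definition should not be left open until results are visible.

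The cost is one phrase and one check of the derivation. Both components are already recorded at each assessment, so no new data are needed.

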#### Health-related quality of life, fatigue and mood

The Functional Assessment of Cancer Therapy-Fatigue (FACT-F) [87] and the Functional Assessment of Cancer Therapy-Prostate (FACT-P) [88] questionnaires will be used to assess fatigue and HR-QoL, respectively. The Assessment of Quality of Life 8D will also be used to assess HR-QoL [89]. The Geriatric Depression Scale will be used to assess depression [90]. The Depression Anxiety Stress Scale 21-item will be used to assess depression, anxiety, stress and psychological distress [91].

#### Anthropometry

Height and body mass will be assessed using a portable stadiometer and scales, respectively. Body Mass Index will be calculated using height and body mass. Girth measurements of the chest, waist and hips will be assessed using standard techniques.

#### Habitual physical activity

The Community Healthy Activities Model Programme for Seniors physical activity questionnaire will be used to assess participation in a comprehensive list of low, moderate and vigorous physical activities [92]. Participants will document the frequency and duration of their participation in a ‘typical week’ of the preceding 4 weeks. The results will be reported as estimated kilojoules per week spent in moderate- to high-intensity activities and hours per week spent undertaking weight-bearing exercise.

#### Diet

Diet will be assessed using a 24-h food recall performed during a one-on-one interview via telephone. Prior to the telephone interview, the participant will complete a 24-h food diary with instructions that will be discussed at the baseline testing session. These instructions will include how to use household measures (e.g. measuring cups, plates, bowls, glasses) to help estimate food portion sizes. In addition, a standard script will be used during the telephone interview to maximise the ability of participants to recall what was consumed. Dietary analysis will be performed using Australia-specific dietary analysis software (FoodWorks, Xyris software, Highgate Hills, QLD, Australia).

#### Additional questionnaires

A demographic, clinical and lifestyle questionnaire will be used to obtain background information from participants (e.g. age, education history, marital status, employment status, cultural background, PCa and ADT-use details). Sun-exposure habits and practices, alcohol consumption, past and current medical conditions, use of prescription and non-prescription medication (type and dose) and falls and fracture history will also be included in the questionnaire.

